
#### Exercise referral and recruitment strategies

When making referrals, participating GPs and specialist physicians will first screen their patients using the inclusion criteria and then send their contact details to the trial staff for enrollment.

The following promotional initiatives will be implemented:

- providing GPs working near the trial areas of the trial with informative material on healthy lifestyle (see below) and asking them to participate in the trial by adopting the ERS; participating GPs will then provide their T2D patients with information on the trial and refer them to the TRIPL-A;

- distributing fliers in the clinical centers and facilities involved in the trial;

- displaying posters in the clinical centers and facilities involved in the trial.

#### Healthy lifestyle informative material

TRILP-A staff will create and make available an “active lifestyle leaflet”, whose purpose is to promote PA in older T2D patients, and a “healthy eating brochure”, whose purpose is to help T2D patients to improve their dietary habits. For this purpose infographic materials from the “Handbook for Canada’s physical activity guide to healthy active living” [27] will be translated into Italian and modified according to the needs of this trial.

The healthy eating brochure will help diabetic patients to improve their dietary habits by balancing meal nutrients composition and making healthy food choices.

### Enrollment and arm assignment

A total of 300 older T2D patients will be enrolled and randomly assigned to either the control or the intervention arm with a 1:1 ratio, using a computerized permuted blocks randomization. The randomizations will be performed using a code created by the statisticians of the INRCA Biostatistical Center, who will not be involved in any other part of the trial. Allocation concealment will be assured because the trial staff will not know the randomization code and procedures (e.g., block sizes), and the allocation will be made only after the termination of all baseline tests (see Fig. 1).

Due to the obvious differences between the interventions (see below), neither staff nor participants will be blinded to group allocation. However, before data analysis, patient allocations and identification numbers will be replaced by categorical variables whose meaning will be unknown to data analysts.

### Intervention

Trial intervention will last 18 months during which time concomitant care will be permitted. Patients of both trial arms will be retained as long as they meet the inclusion and exclusion criteria.

#### Intervention arm

Patients assigned to the intervention arm will receive the healthy lifestyle informative material and a behavioral counselling on physical activity and diet by a trained physician. The healthy lifestyle informative material will be given to the patients during the behavioral counseling and discussed.

A structured exercise program of 18 months, with alternating three-month periods of supervised and non-supervised training (i.e., discontinued supervision), will be implemented. Participants will train three times per week, with at least 48 h between each exercise session.

During the 3 three-month periods of supervised training (period 1: 1st to 3rd month; period 3: 7th to 9th month; period 5: 13th to 15th month), patients will exercise at a fitness center under the supervision of an exercise specialist, who will use the WBA to constantly monitor and update the exercise prescription. In the non-supervised training periods (period 2: 4th to 6th month; period 4: 10th to 12th month; period 6: 16th to 18th month) participants will train on their own and use the WBA to access their aerobic training schedule and parameters (duration and intensity). They will also be asked to enter the actual workout performed into the WBA at the end of each self-monitored exercise session.

The aerobic exercise training protocol will be designed according to the internationally accepted recommendations and guidelines on health-enhancing PA for older adults [28–30] and T2D patients [31–34].

Aerobic exercise intensity will be prescribed and monitored according to heart rate (HR), which is a reliable parameter in the present trial since patients will not be taking any medication that could affect it. For each patient, the percentage of target HR (%HR_target_) prescribed for a given exercise period will be applied to the HR reserve (HRR), i.e. the difference between resting HR (HR_rest_) and maximum HR (HR_max_). Patients’ HR_rest_ will be directly measured, whereas the HR_max_ will be estimated according to the equation proposed by Gellish et al. [35]. For each patient, the exercise session target HR (HR_target_) will then be calculated (in beats per minute) as follows: HR_target_ = [(HR_max_ – HR_rest_) x %HR_target_] + HR_rest_. This approach, namely the “HRR method” [36], is widely accepted as the most accurate in establishing a HR_target_ because, i) it accurately reflects the percentages of the reserve values of oxygen uptake (*V̇*O_2_R), i.e. the gold standard for assessing the relative metabolic intensity, and ii) it allows the correction of the exercise intensity for the HR_rest_, which can be highly variable among subjects [37].

#### Supervised exercise

Aerobic exercise intensity and duration will gradually increase throughout each three-month period (see Table 1).

**Table 1 Tab1:** Supervised aerobic training rate of progression for exercise session intensity and duration parameters

	Period 1	Period 3	Period 5
Intensity (%HRR range)	40–50	45–55	50–60
Duration (minute range)	20–30	30–40	40–50

Notes: Values are indicative and will be modified according to patient’s response to exercise; %HRR, heart rate reserve percentage

At the end of each session, the exercise specialist will prescribe the exercise duration and intensity of the next session, aiming for a progression rate that will allow patients to reach the upper limit range of each three-month period at least one week before its end. The WBA will help the exercise specialist to implement the progression rate by highlighting: 1) when the patient has completed two consecutive training sessions; 2) the duration and intensity of the previous sessions; 3) the pattern of the previous increases in duration and intensity (in order to alternate the type of increment); 4) the type of exercise (e.g. treadmill, bike, etc.) performed in the previous sessions (which will also be alternated).

The *10-point category ratio scale* (CR-10) of perceived exertion [38] will also be also used to monitor exercise intensity. In order to familiarize participants with the scale, the exercise specialist will 1) provide them with standardized instructions on how to use it, and 2) anchor the upper limit of the scale to a specific feeling experienced in the past during intense PA sessions (i.e., anchoring memory procedure).

### Non-supervised exercise

Aerobic exercise intensity and duration achieved at the end of each supervised three-month period will be used as a reference for the subsequent non-supervised period (see Table 2). Patients will choose the type of aerobic exercise independently but will be required to adhere to the exercise intensity and duration prescribed for that particular three-month period. When patients are not be able to monitor their own exercise HR while exercising, they will be required to control for exercise intensity by trying to achieve the same rate of perceived exertion of the last session of the previous supervised training period. They will also be asked to enter exercise duration, average HR and perceived exertion into the WBA after each training session.

**Table 2 Tab2:** Non-supervised aerobic training rate of progression for exercise session intensity and duration parameters

	Period 2	Period 4	Period 6
Intensity (%HRR target)	50	55	60
Duration (minutes)	30	40	50

Notes: %HRR, heart rate reserve percentage

#### Control arm

Patients assigned to the control arm will only receive the healthy lifestyle informative material and a behavioral counselling session on physical activity and diet by a trained physician. The healthy lifestyle informative material will be discussed with the patients and handed out to them during the behavioral counselling session.

### Intervention adherence

Three main strategies will be used to improve intervention adherence throughout the trial. Firstly, the healthy lifestyle informative material will be handed out and discussed with all participants at every follow-up. Secondly, periodic feedback (about twice during each three-month period) will be given to the intervention arm participants (by e-mail and/or by telephone). The feedback will be based on training adherence data retrieved from the WBA: acceptable adherence will be reinforced, whereas participants whose adherence has decreased will be provided with motivational inputs. Lastly, intervention arm patients will be contacted by phone each time they attend one fewer session per week than expected for two consecutive weeks.

### Assessments/outcomes

Patients’ anthropometrics, sedentary habits, PA level, fitness status, metabolic profile, psychological well-being, quality of life, and use of health-care resources will be assessed, along with other routine assessments, on four separate occasions: at baseline and at 6, 12, and 18 months from baseline (see Table 3). The difference between the intervention and control arms at the 12-month time-point will be considered the main outcome for each measure.

**Table 3 Tab3:** Timing of study assessments

	Screening	Visit 1 baseline	Visit 2 follow-up 1	Visit 3 follow-up 2	Visit 4 follow-up 3
Weeks from randomization	-2	0	24	48	76
Visit window in weeks	–	+ 2	+/− 2	+/− 2	+/− 2
Informed consent	X				
Demographics	X				
Inclusion/exclusion criteria	X	X			
Anthropometric measures		X	X	X	X
Clinical variables		X	X	X	X
Randomization		X			
Lifestyle counseling		X			
Lifestyle informative material		X			
WBA training (only for intervention group)		X			
Blood pressure		X	X	X	X
Registration of laboratory assays		X	X	X	X
LDCW		X	X	X	X
IPAQ (short form)		X	X	X	X
EQ-5D-5L		X			X
PSQI		X			X
Healthcare resource consumption		X	X	X	X
Events					
Adverse events including hypoglycemia		X	X	X	X
New diagnoses		X	X	X	X
Intervention compliance check			X	X	X
Trial completion					X

Notes: *LDCW* long distance corridor walk, *IPAQ* International Physical Activity Questionnaire, *EQ-5D-5L* Euro Quality of Life 5 Dimensional questionnaire, *PSQI* Pittsburgh Sleep Quality Index

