#### Data analyses

*Intention to treat* analysis will be adopted to account for possible issues related to noncompliance and missing outcomes. Data quality and internal consistency will be assessed *ex-post* using Cronbach’s alpha. In addition, automatic routines will be performed on the data to detect possible outliers, which will be excluded from further analyses. Explorative univariate and bivariate data analyses will then be performed.

For each study outcome, the intervention and control arm will be compared, as the difference between baseline and 12-month time-point, using independent sample t-tests. A mixed-design ANOVA will be used to compare each study outcome between intervention and control arm at the four different time-points, followed by *post-hoc* pairwise comparisons when a significant interaction is found. Participants’ characteristics (e.g., age, sex, fitness status, physical activity level, and metabolic profile) will be used as covariates, and appropriate interaction terms will be assessed and may be included in the model. For all tests, 2-sided *p* values with an α level of significance of 0.05 will be used. Bonferroni’s criterion will be used to adjust the overall α level to correct for multiple tests.

The assumptions of each statistical test will be assessed before analyses and, if not met, either data transformation will be performed or alternative statistical methods will be adopted (e.g., GEE, mixed-models, non-parametric analyses, etc.) will be performed. The residuals and goodness of fit of the models will also be examined.

SPSS Statistics (IBM) and R (R Core Team) software will be used to perform data analyses.

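### Table 3 schedules the EQ-5D-5L and PSQI only at baseline and 18 months, so the 12-month and four-time-point analyses promised for every outcome cannot be run for them

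*Protocol article*

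**What the plan says.** Under Assessments/outcomes, the protocol article lists the domains to be measured, quality of life among them, and says that they are assessed "on four separate occasions: at baseline and at 6, 12, and 18 months from baseline (see Table 3"). The next sentence sets the main comparison: "The difference between the intervention and control arms at the 12-month time-point will be considered the main outcome for each measure".

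The Data analyses section carries this into the tests. First: "For each study outcome, the intervention and control arm will be compared, as the difference between baseline and 12-month time-point, using independent sample t-tests". Then: "A mixed-design ANOVA will be used to compare each study outcome between intervention and control arm at the four different time-points". Neither sentence exempts any outcome.

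Table 3 gives the schedule that sites would work from. The row for the primary outcome instrument has four marks: "IPAQ (short form) X X X X". The EQ-5D-5L and PSQI rows have two marks each, at Visit 1 and Visit 4, with Visits 2 and 3 blank. The timing rows read "Weeks from randomization -2 0 24 48 76" and "Visit window in weeks – + 2 +/− 2 +/− 2 +/− 2".

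**The concern.** The text and the table it cites disagree on when two questionnaires are given. The text requires a 12-month value for each measure, and the table does not collect one for these two. Quality of life is a named secondary objective, so its stated main analysis would have no data.

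A questionnaire that was not given at a visit cannot be recovered afterwards. The analysts would have to choose another time-point for these outcomes, in practice 18 months. Unless that choice is written down beforehand, it will be made in an open-label trial after results for other outcomes may be known.

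A smaller concern is that the visit weeks in Table 3 do not line up consistently with the months used in the text, the sample size calculation and the tests.

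**Working it through.** **1. Schedule against planned analyses.** The marks are from Table 3. The requirements are from Assessments/outcomes and Data analyses.

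| Measure | Visit 1 (week 0) | Visit 2 (week 24) | Visit 3 (week 48) | Visit 4 (week 76) | 12-month t-test possible? | Four-time-point ANOVA possible? |
|---|---|---|---|---|---|---|
| IPAQ (sitting time, MET) | X | X | X | X | yes | yes |
| LDCW, laboratory assays, anthropometry, blood pressure, healthcare use | X | X | X | X | yes | yes |
| EQ-5D-5L (score and visual analogue scale) | X | – | – | X | no | no |
| PSQI | X | – | – | X | no | no |

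For the last two rows, the planned 12-month observations are 0 and the occasions available are 2 of 4. A misread table is an unlikely explanation: the other outcome rows show four marks in the expected columns, and the two questionnaire rows share one pattern.

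**2. Sample size.** It rests only on sitting time at 12 months (SD 200, difference 75 min/day, two-sided alpha 0.05, power 0.80):

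n = 2 × [200 × (1.960 + 0.842) / 75]² = 111.6, so 112 per arm, as the plan states.

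Sitting time is collected at Visit 3, so nothing here changes.

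**3. Visit weeks against months.** Three conventions were tried: calendar months (365.25 / 12 / 7 = 4.348 weeks), 52/12 weeks, and 4 weeks.

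| Visit | Window (weeks) | Stated month | Calendar | 52/12 | 4-week |
|---|---|---|---|---|---|
| 2 | 22–26 | 6 | 26.09 (just out) | 26.0 (on edge) | 24 (in) |
| 3 | 46–50 | 12 | 52.18 (out) | 52.0 (out) | 48 (in) |
| 4 | 74–78 | 18 | 78.27 (just out) | 78.0 (on edge) | 72 (out) |

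No convention fits all three visits: 52/12 fails at Visit 3, four-week months fail at Visit 4, and calendar months miss all three, two of them by under 0.3 week. In calendar months, Visit 3 spans 46/4.348 = 10.6 to 50/4.348 = 11.5 months. It closes 52.18 − 50 = 2.2 weeks before 12 months (2.0 weeks with 52/12). The text counts months from baseline and Table 3 counts from randomization. Even with baseline two weeks before randomization, 12 months falls at week 52.18 − 2 = 50.18, still just outside.

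On the other hand, the 12th month runs from week 11 × 4.348 = 47.8 to week 52.2. The nominal week 48 and the window up to week 50 lie within it.

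**The case against.** The strongest reply is that Table 3 may show the real intention: the two questionnaires are given only at the start and the end to limit burden, and the general sentences were not meant to reach them. That is plausible, and a baseline-to-18-month comparison would survive. But the article says nowhere that this is so, and for quality of life it says the opposite by listing it among the domains assessed on four occasions. The contradiction stands whichever side was intended.

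For the PSQI the conflict is weaker. The article describes it as a measure of sleep disorders, and sleep is not in the four-occasion list. A reader might infer that the PSQI is the measure of psychological well-being, which is in the list, but no section says so. The conflict for the PSQI rests only on the wording that covers every measure and every study outcome. That wording is enough, but it is less direct than for the EQ-5D-5L.

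A reader might also infer that Table 3 defeats the 12-month comparison for all measures, or that the primary outcome is lost because the Visit 3 window stops short of 52 weeks. The documents do not support either. IPAQ is marked at Visit 3. That visit is plainly the nominal 12-month visit, it is timed alike in both arms, and it overlaps the 12th month. No between-arm bias or loss of power follows from the timing.

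Moving Visit 3 to week 52 with the same ±2 weeks has its own difficulty. The window would run to week 54, about 54 − 52.2 = 1.8 weeks into supervised period 5, which starts with the 13th month.

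**Conclusion.** The contradiction is real and confined to two secondary questionnaires. Under Table 3, neither the baseline-to-12-month t-test nor the four-time-point ANOVA can be carried out for the EQ-5D-5L score, its visual analogue scale or the PSQI. This assumes that sites follow the table. If they follow the text, 12-month data would exist, at least for quality of life, so it cannot be stated as fact that no patient will have them.

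The primary outcome, the other measures marked at all four visits, and the sample size are untouched. The mismatch between weeks and months is a minor inconsistency: the last allowed day of Visit 3 is about 2 weeks short of 52 weeks, with no demonstrated effect on the comparison. Overall this should be fixed, because stated main analyses have no data under the stated schedule, but it is not critical to the trial's main conclusion.

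**What to change.** Reconcile the text and Table 3 in one of two ways, and record the choice before outcome data are examined.

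- **Add the assessments.** Mark the EQ-5D-5L and PSQI at Visits 2 and 3. The planned analyses then stand as written. The cost is two short questionnaires at two visits that already take place. The trial was registered retrospectively, which suggests that enrolment had begun. Visits already passed cannot be recovered, so early participants may lack these values.
- **Restate the time-point.** Keep Table 3, name 18 months as the main time-point for these two questionnaires, analyse them as a baseline-to-18-month comparison, and exclude them from the 12-month t-test and the four-time-point ANOVA. The sentences covering every measure and every outcome then need a stated exception. The cost is a text edit and no information on these outcomes at 6 and 12 months.

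Separately, reconcile the visit weeks with the stated months: either define the month convention or revise the weeks, with windows that do not run into the next supervised period. This is a table edit if no visits have been scheduled yet. Otherwise, stating the actual timing of each visit is sufficient.

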#### Primary outcome measure

Sitting time will be retrieved from the results of the IPAQ short form and computed as average daily minutes of sitting calculated over a one-week period. The IPAQ is a well validated tool [39–43] for assessing both habitual sitting time and physical activity engagement. The IPAQ short form will be interview-administered by trained personnel.

#### Secondary outcome measures

##### Physical activity level and fitness status

Metabolic Equivalents (MET) per week (an index of physical activity level) will be calculated using the IPAQ short form. Maximal oxygen uptake (*V̇*O_2max_; an index of fitness status) will be calculated using the results of the Long Distance Corridor Walk (LDCW) test and expressed as the sex- and age-specific reference percentile for *V̇*O_2_max [34]. The LDCW has been validated as a reliable shuttle test to estimate *V̇*O_2max_ in subjects between 60 to 91 years of age [44, 45]: after a warm-up of two minutes, the participant is asked to walk 10 laps “as quickly as possible”, over a 20-m course marked with cones (i.e., 400 m).

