#### Inclusion criteria

Patients who meet all of the following criteria will be recruited:

- age range (years): 65 to 74;

- suffering from T2D according to ADA criteria [25];

- physically inactive or insufficiently active (i.e., level 1 or level 2 exposure to physical inactivity) according to the WHO framework of health risks quantification [26], as assessed using the results of the *International Physical Activity Questionnaire* (IPAQ) short form.

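### Fitness is named only as a reference percentile of VO2max, so equal gains count unequally and power may fall if patients lie low in the reference

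*Protocol article*

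**What the plan says.** In the Protocol article, under Physical activity level and fitness status, VO2max "will be calculated using the results of the Long Distance Corridor Walk (LDCW) test". It is then "expressed as the sex- and age-specific reference percentile". No fitness outcome in units of oxygen uptake is named.

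The Data analyses section treats every study outcome the same way: "the intervention and control arm will be compared, as the difference between baseline and 12-month time-point, using independent sample t-tests". A mixed-design ANOVA over the four time-points follows, with participant characteristics ("age, sex, fitness status, physical activity level, and metabolic profile) will be used as covariates"). The Assessments/outcomes section makes the between-arm difference at 12 months the main result for each measure.

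Under Inclusion criteria, patients must be "physically inactive or insufficiently active" by questionnaire, with "age range (years): 65 to 74". Measured fitness is not an entry criterion.

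**The concern.** A percentile is a bounded, nonlinear function of VO2max. If the reference distribution is bell-shaped, the scale is steep near the median and flat in the tails. A t-test or ANOVA on percentiles treats each point as equal, although a point in the lower tail represents a larger gain in oxygen uptake than a point near the median.

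The trial recruits inactive older people with type 2 diabetes. If many of them sit low in the reference, their improvement counts for little in the mean and the comparison loses power. The effect is also harder to express as a change in oxygen uptake. The purpose of the conversion, removing age and sex differences, can be met by covariates that the plan already names.

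**Working it through.** **The plan's own figure.** The only sample size is for sitting time: difference 75, SD 200, two-sided α 0.05, power 0.80. Recomputed, this gives 112 per arm, as stated. The evaluable number is 300 × 0.8 / 2 = 120 per arm. No power is claimed for fitness.

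**Inputs for the fitness check.** From the article: 120 per arm, α 0.05, t-test on baseline to 12-month change. Assumed, because the article gives no figures:
- normal reference distribution, percentile = 100·Φ(z), where z is VO2max in reference SDs;
- trial SD 0.8 reference SD;
- baseline to 12-month correlation 0.7;
- a constant effect giving about 82% power on the VO2max scale;
- the location of the mean patient, varied from 0 to −2 SD.

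**Effect implied.** SD of change = 0.8 × √(2 × (1 − 0.7)) = 0.620. Standard error = 0.620 × √(2/120) = 0.080. An effect of 0.23 reference SD gives 0.23/0.080 = 2.875, and power ≈ Φ(2.875 − 1.96) = Φ(0.915) ≈ 0.82.

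**Shape of the scale.** The slope relative to the median is φ(z)/φ(0). The value of a 0.25 SD gain is 100 × [Φ(z + 0.25) − Φ(z)].

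**Power.** Simulated t-test on change, 20,000 trials per location. The VO2max scale gives about 82% throughout.

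| Mean patient (reference SD) | Percentile | Relative slope | 0.25 SD gain, points | Power on percentile | Loss, points |
|---|---|---|---|---|---|
| 0 | 50 | 1.00 | 9.9 | 79% | about 2–3 |
| −0.5 | 31 | 0.88 | 9.3 | 79% | about 2–3 |
| −1 | 16 | 0.61 | 6.8 | 76% | about 5–6 |
| −1.5 | 7 | 0.32 | 3.9 | 70% | about 12 |
| −2 | 2 | 0.14 | 1.7 | 60% | about 21 |

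**Sensitivity.**
- *Table floor.* If the lowest tabulated value is the 5th percentile, power at −0.5, −1, −1.5 and −2 SD is about 78–79%, 74–75%, 63% and 46–47%.
- *Other inputs.* With an effect of 0.31 trial SD and a trial SD of 0.5 or 1.0 reference SD, VO2max against percentile power is 0.86–0.87 against 0.81–0.86 at the 50th percentile. It is 0.86–0.87 against 0.80–0.85 at the 16th, 0.85–0.88 against 0.74–0.81 at the 7th, and 0.85–0.87 against 0.64–0.74 at the 2nd.

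**With covariates.** VO2max adjusted for baseline and sex has about 87% power at every location. The percentile adjusted in the same way has about 85%, 84%, 81%, 75% and 65% from 0 to −2 SD. The loss from the scale is therefore much the same as in the table. Baseline adjustment adds about 5 points on either scale and is a separate gain.

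**Unadjusted 12-month values.** Here the order can reverse. With an assumed sex difference of 1 reference SD, unadjusted VO2max has about 47% power. The percentile has about 58% at −0.5 SD, falling to about 45% at −2 SD. With a 1.5 SD sex difference the figures are about 37% against about 45% to 58%, and the percentile wins at every location. With no sex difference VO2max wins. For change scores, a stable sex difference cancels.

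**The case against.** The strongest reply is that the size of the harm depends on a reference table and a fitness distribution that the article does not give. Entry is by questionnaire inactivity, not measured fitness. The Background says most older people are sedentary, so an inactive patient need not lie far down an age-specific reference. The exclusions for lung disease and severe cardiovascular disease remove some of the least fit. All of this stands. A reader might infer that the trial mean lies deep in the lower tail and that the large losses apply. The article does not support that; near the median the loss is small.

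A second reply is that the percentile does useful work. A reader might infer that changing to raw units costs nothing. It does not hold for an unadjusted 12-month comparison, where raw VO2max carries sex and age variation that the percentile removes. The Assessments/outcomes section puts the emphasis on the 12-month difference, and the covariates are named after the ANOVA and are not tied to the t-test. This also stands, and it is why the change of scale must come with covariates.

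Third, a percentile change has meaning: it is a shift in standing against peers of the same age and sex. It would be too strong to say that it tells nothing about fitness.

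Fourth, the plan checks test assumptions and allows transformation or other methods. That is a partial safeguard. It acts only if assumptions are judged to fail, does not name raw VO2max, and a test on percentiles can lose power without failing such a check.

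Finally, analysis detail may sit in a document not shown. But the outcome scale is stated here, so this is a choice made and not a detail left out.

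**Conclusion.** The point holds as an improvement to a secondary outcome. The article fixes a bounded, nonlinear scale as the only named form of the fitness outcome and analyses it by differences in means. The direction follows from any bell-shaped reference: gains far below the median count for less. On the planned change-score test the percentile did not outperform VO2max at any location examined beyond simulation error.

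The size is conditional. Under the assumed inputs the loss is about 2 to 6 points of power with the mean patient at 0 to −1 SD, and about 12 to 21 points at −1.5 to −2 SD. Which range applies cannot be read from the article. These figures use α 0.05 without the planned Bonferroni adjustment.

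A reader might go further and infer that the fitness comparison is biased or invalid. It is not: randomisation protects it on either scale. The primary sample size reproduces and is untouched.

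**What to change.** State in the outcome and Data analyses sections that fitness is analysed as estimated VO2max in its own units, with baseline VO2max, age and sex as covariates. The covariates are part of the fix: without them, a 12-month comparison of raw VO2max gives up the standardisation that the percentile supplies. Keep the reference percentile as a descriptive figure by arm and visit.

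The cost is a sentence or two. VO2max is already calculated at each assessment, and age and sex are already named as covariates, so no new data or visits are needed. The change should be made before outcome data are examined by arm.
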